### Participant Recruitment

#### Prospective Study

We will recruit participants for whom a decision has already been made to initiate warfarin by the managing clinician (Figure 2). Decisions regarding whether or not patients require inpatient management for the initiation of warfarin are also made by the managing clinician. Participants who meet the inclusion criteria will be consecutively screened and enrolled in the study. In cases where participants are discharged from the hospital and referred for follow-up in a clinic close to their home or in the outpatient clinic of the hospital, the clinical records used at the recruitment site and those at the referral clinic will be reviewed.

The participant’s first 3 days of dosing will be driven by our new algorithm (Multimedia Appendix 1). Thereafter, dose revisions will be made according to current guidance outlined in the “Standard Treatment Guidelines and Essential Medicines List for South Africa” [11]. We will repeat the INR of participants every 2-4 days until stability is reached (2 consecutive INRs are in the target range). We will ensure close monitoring during the first 14 days of treatment. If stability is reached before the 14th day, we will continue to closely monitor the patient for the first 14 days. If the participant has not reached stability at 14 days, we will continue to monitor the participant with INRs every 2-4 days and adjust the warfarin dose until stability is reached. As we measure participants’ INR every 2-4 days over this period of close follow-up, we will propose dose adjustments to the clinical team based on INR results. The clinical team will still be free to override proposed adjustments based on their clinical expertise. Once stability is reached, we will perform one more INR 1 week later, after which the participants’ care will be fully handed back to the clinical team, and participants will continue to follow-up according to the local standard of care. We will continue to monitor and record all consecutive INR results for 3 months through direct contact with the participant at outpatient clinic, home visits, or electronic or paper record review.

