### Withdrawal Criteria

A participant can withdraw from the study at any time if it is his or her wish or if it is medically necessary, as judged by the Investigator. A participant will be withdrawn if any of the following applies:

Voluntary discontinuation by the participant, who is at any time free to discontinue their participation in the study without prejudice to further treatment.Incorrect enrollment of the participant (ie, the participant does not meet the required inclusion and exclusion criteria).Participant fails to comply with the protocol requirements or fails to cooperate with the investigator.Participants experiencing severe adverse events who return to standard care.

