### Study Outcomes

The primary outcome for this study is TTR over the initial 3 months of warfarin therapy, which we will measure using the Rosendaal linear interpolation method [14]. We will compare time in the therapeutic INR range between the prospectively followed participants who receive the warfarin bundle and a retrospectively reviewed patient group. This will yield an estimate of the impact of the warfarin care bundle as a whole. It will not be possible to distinguish the effect of the individual components of the warfarin bundle on TTR.

The secondary outcomes include time to achieve therapeutic INR and number of adverse events (death, bleeding, or thrombosis), which will be compared between the prospectively followed-up participants and the retrospectively reviewed patient group. We will also explore staff and patient experiences and acceptability of the warfarin bundle using in-depth interviews or focus group discussions and conduct an economic analysis of the cost-effectiveness of the warfarin bundle. In addition, we will perform a qualitative assessment of useful lessons from the RCA.

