### Data Analysis Plan

For the prospective and retrospective studies, all statistical analyses will be undertaken in R. For determining percentage time in target range for each participant, all INR measurements during the first 12 weeks as well as the first INR measurement after the 12-week time point will be used, and the method of Rosendaal et al [14] will be applied. Percentage TTR will be compared between the prospective implementation group and the retrospective standard of care group using the Student *t* test. Time to achieving target INR (defined as the first of at least two INR measurements in range at the same dose) will be compared between the prospective and retrospective groups using the log-rank test (to compare the survival distributions of the 2 groups, and these will be calculated using the Kaplan-Meier estimator). Adverse events will be compared between the 2 groups using a chi-square test. A significance threshold of *P*<.05 will be applied.

The primary analysis will include all participants who remain in the project for at least 2 weeks (14 days). Our primary analysis will include only patients who have at least two weeks’ follow-up, since it is unlikely that those with less than 2 weeks’ follow-up will have sufficient information on INR measurements for TTR to be reliably estimated. A sensitivity analysis will be undertaken, including only participants who have completed 12 weeks (84 days) of follow-up.

We will also conduct both an intention-to-treat analysis (including all recruited patients) and a per-protocol analysis (excluding patients where health care provider decided to reject the dose recommended by the dosing algorithm). The project will follow national guidelines for best practice and be guided by local policy. Relevant data will be made openly available to other researchers in a timely way (after primary outputs are published) with as few restrictions as possible unless we are protecting intellectual property, respecting confidentiality, or honoring third-party agreements. The program management board will review access to data and will provide a governance mechanism.

We will perform a secondary analysis comparing the primary and secondary outcomes between retrospective controls from the pre–COVID-19 and COVID-19 periods to measure the impact of the pandemic on anticoagulation control.

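### Kaplan-Meier curves for time to target INR overstate the share reaching target if patients who die or permanently stop warfarin first are censored; cumulative incidence curves would avoid this (minor, secondary outcome)

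*Protocol article*

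**What the plan says.** The Data Analysis Plan of the protocol article gives the endpoint as "Time to achieving target INR (defined as the first of at least two INR measurements in range at the same dose". The two groups are compared by a "log-rank test (to compare the survival distributions of the 2 groups, and these will be calculated using the Kaplan-Meier estimator". No other estimator is named for this endpoint. No rule says what happens to a patient who dies or stops warfarin before target.

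Study Outcomes shows that the endpoint is secondary and that death is expected: "The secondary outcomes include time to achieve therapeutic INR and number of adverse events (death, bleeding, or thrombosis". Death enters the plan only through a separate comparison: "Adverse events will be compared between the 2 groups using a chi-square test".

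Under Withdrawal Criteria, one reason for leaving the study is "Participants experiencing severe adverse events who return to standard care". Nothing there says that warfarin is stopped, or how such a participant enters the time-to-target analysis.

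**The concern.** Kaplan-Meier recognises one type of event. In ordinary use, anyone who leaves the risk set without that event is censored, and the curve assumes that they would have gone on to reach target at the same rate as those still observed. That is reasonable for a patient whose records stop. It is not reasonable for a patient who has died or will take no more warfarin, because that patient cannot reach target.

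The consequence is one-directional. 1 minus Kaplan-Meier then estimates the share who would reach target if nobody died or stopped, which is at least as large as the share who do reach it. The excess grows with the rate of competing events. The protocol's own rationale links poor anticoagulation control to bleeding, thrombosis and death, and expects the bundle to improve control. Equal rates in the two groups therefore cannot be taken for granted, and the two curves may be raised by different amounts.

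**Working it through.** The protocol states no expected share reaching target, death rate or stopping rate, so there is no figure of its own to reproduce. The calculation below is an illustration on assumed rates.

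**Inputs from the document.** Follow-up is 84 days. The groups are 304 controls and 152 bundle patients (Sample Size and Power Calculations). Table 1 gives 330 controls, which does not change the rounded results.

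**Assumptions.** p is the value of 1 minus Kaplan-Meier at day 84, that is, the share reaching target if there were no competing events. d is the 84-day risk of death or permanent stopping if target were never reached.

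**Formulas, constant hazards.**
- Hazard of target: h = −ln(1−p)/84
- Hazard of death or stopping: g = −ln(1−d)/84
- Share actually reaching target: CIF = h/(h+g) × [1 − (1−p)(1−d)]
- Overstatement: p − CIF

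**Worked case, p = 0.70 and d = 0.10.**
- h = 1.20397/84 = 0.014333 and g = 0.10536/84 = 0.001254
- h/(h+g) = 0.9195
- 1 − 0.30 × 0.90 = 0.730
- CIF = 0.9195 × 0.730 = 0.671, so 0.700 overstates by 2.9 points

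**Range, constant hazards (overstatement in points).**

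| d | p = 0.60 | p = 0.75 | p = 0.90 |
|---|---|---|---|
| 2% | 0.5 | 0.6 | 0.6 |
| 5% | 1.3 | 1.5 | 1.5 |
| 10% | 2.6 | 3.0 | 3.0 |
| 20% | 5.3 | 6.1 | 6.1 |

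**Effect of timing, p = 0.70.** An early hazard is taken proportional to exp(−t/14) and scaled to the same 84-day total. The CIF is then integrated numerically.
- Competing events early, target constant, d = 10%: 5.4 points.
- Target early, competing events constant: 0.87 points at d = 10%, 0.43 at 5% and 0.25 at 3%.
- Both early, d = 10%: 2.9 points, as with both constant.

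**Between-group distortion.** Take p = 0.70 in both groups, so that the Kaplan-Meier curves coincide, with d = 10% in controls and 5% in bundle patients.
- For d = 5%: g = 0.05129/84 = 0.000611, and CIF = 0.9591 × (1 − 0.30 × 0.95) = 0.9591 × 0.715 = 0.686.
- Hidden difference: 0.6858 − 0.6713 = 0.0145, or about 1.5 points.
- SE of the difference: √(0.671 × 0.329/304 + 0.686 × 0.314/152) = √(0.000726 + 0.001417) = 0.046, or 4.6 points.
- Ratio: 1.45/4.6 = about 0.3 SE.

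If target is reached early, the hidden difference falls to 0.44 points, about 0.1 SE. An unfavourable case, with risks of 10% against 3% and early competing events, gives 3.8 points against an SE of about 4.7, or 0.8 SE.

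**The case against.** The strongest reply is that the article never says these patients are censored. That is correct. A reader might infer a written rule, but the document names the estimator and stays silent on the rule. If such patients were kept in the risk set without an event to day 84, and there were no other losses, Kaplan-Meier would give the right share. The full protocol or analysis plan may say so. What remains is that the article does fix the estimator, and its ordinary use censors these patients. The point concerns that choice, not a missing detail.

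A second reply is that the planned inference is the log-rank test and that no share reaching target is promised as a result. This also stands in part. A reader might infer that the test is invalid. It is not: with competing events censored, and other censoring independent, it validly tests equal cause-specific hazards of reaching target. Gray's test answers a different question and would let a difference in mortality show up as a difference in INR attainment. The flaw is confined to the curves and to any proportion read from them.

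A third reply is that withdrawal after a severe adverse event is not a competing event. This stands in full. Return to standard care does not mean that warfarin stops, and such a patient may still reach target. Censoring at withdrawal may be informative, but that is a separate matter that cumulative incidence curves do not solve.

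Finally, the Data Analysis Plan says: "The primary analysis will include all participants who remain in the project for at least 2 weeks (14 days". If that set also serves this endpoint, which the text leaves unclear, patients who die before day 14 are excluded, not censored, and the 5.4-point case does not apply as computed. Later deaths remain, and the planned analysis of all recruited patients brings the early ones back.

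**Conclusion.** The concern holds for the curves. Death or permanent stopping of warfarin can prevent the event, and the estimator named has no place for either. Under its ordinary use the displayed share reaching target is too high. With constant hazards and assumed competing risks of 2% to 10%, the excess is about 0.5 to 3 points per group. Early attainment of target reduces it to about 0.3 to 0.9 points at risks of 3% to 10%, and early competing events at 10% raise it to 5.4 points. All these rates are assumptions.

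A reader might conclude that the comparison between groups is seriously biased. The documents do not support that. They give no rates, and in the cases worked here the distortion is 0.1 to 0.3 SE of the difference at 10% against 5%, and 0.8 SE in the unfavourable case. With the same competing risk and the same hazard of target in both groups, both curves are raised equally. Severity is minor: the outcome is secondary and the stated test stands.

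**What to change.** In the Data Analysis Plan:
- Replace the Kaplan-Meier curves for time to target INR with Aalen-Johansen cumulative incidence curves, treating death and permanent stopping of warfarin before target as competing events. Keeping these patients event-free in the risk set to day 84 gives the same share if there is no other loss to follow-up; with other losses, Aalen-Johansen is the safer choice.
- Report the number and cumulative incidence of the competing events by group.
- Keep the log-rank test, labelled as a comparison of the cause-specific hazard of reaching target. Gray's test may be added as a supplement.
- State separately how participants withdrawn after a severe adverse event enter this analysis, since that is a question of possibly informative censoring.

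The cost is a sentence or two and a few lines of R, which is already the planned software. Adverse events and dose changes are already collected in both groups, so no new data items are needed. The downside is that the displayed share reaching target becomes slightly less favourable.

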#### Retrospective Review of Patients’ Clinical Records

The following data will be collected from clinical records: age, sex, weight, indication for anticoagulation, target INR range, HIV status, recruitment center, all INR measurements during the first 3 months, any dose changes, and any hospitalizations or adverse events. If participants in the retrospective review were initially hospitalized and then discharged, the recruitment hospital site clinical records as well as the clinical records at the referral clinic will be reviewed.

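### The adverse-event comparison rests on a chi-square test that ignores time at risk and sets study-recorded events against chart-recorded ones

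*Protocol article*

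**What the plan says.** The Objectives section makes fewer adverse effects under the bundle a secondary objective. Study Outcomes names the measure as the "number of adverse events (death, bleeding, or thrombosis), which will be compared between the prospectively followed-up participants and the retrospectively reviewed patient group". The Data Analysis Plan then fixes the method: "Adverse events will be compared between the 2 groups using a chi-square test". The threshold is P<.05. The sentence does not say whether patients or events are counted, and it mentions neither time at risk nor adjustment.

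The same section sets the analysis populations. The primary analysis takes participants with 14 days or more of a 12-week window. The intention-to-treat analysis takes everyone recruited. The third set is described thus: "A sensitivity analysis will be undertaken, including only participants who have completed 12 weeks (84 days) of follow-up". The section does not say which set the adverse-event comparison uses. The Withdrawal Criteria allow follow-up of a prospective participant to end after a severe adverse event.

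The two groups have different sources of events. In the prospective group, INR is measured every two to four days until stable and contact stays close through day 14 (Prospective Study). All adverse events are recorded and assessed for causality (Adverse Events). For controls, "any hospitalizations or adverse events" are taken from clinical records (Retrospective Review of Patients’ Clinical Records).

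**The concern.** A chi-square test treats a patient observed for 14 days and one observed for 84 days as equally exposed. If mean follow-up differs between the groups, the test responds to that difference as well as to risk. The same paragraph uses Kaplan-Meier estimates and a log-rank test for time to target INR, so it handles censoring for that secondary outcome but not for safety.

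The second problem is detection. A minor bleed mentioned at a study contact is recorded, whereas the same bleed in a control counts only if someone wrote it in the chart.

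The third is conditional. If events are entered instead of patients, one patient can contribute several and the observations are no longer independent.

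At stake is the stated secondary question of whether the bundle reduces adverse effects. A significant result in either direction could reflect observation time or detection and not risk.

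**Working it through.** The article gives no event rate, power or size for adverse events, so there is no figure of its own to reproduce. The check asks how far the planned test departs from 5% under stated assumptions.

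**Inputs from the article.** Group sizes are 304 controls and 152 prospective (Sample Size and Power Calculations). The window is 84 days and the threshold is P<.05. Table 1 lists 330 controls and Results reports 167 recruited; using those sizes changes no conclusion below.

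**Assumed inputs.** The 12-week control risk p is 10% or 20%, the event hazard is constant, and records capture a share c of control events. Mean follow-up is f0 (control) and f1 (prospective), and r is the true rate ratio.

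**Formulas.** Expected observed risk, counting patients with at least one event:
- control: 1 − (1 − p)^(c × f0/84)
- prospective: 1 − (1 − p)^(r × f1/84)

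Example with p = 10%, c = 0.80 and 84 days in both groups: control risk is 1 − 0.9^0.8 = 0.081 against 0.100, a ratio of 1.24.

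**No true difference (r = 1), uncorrected chi-square, 40,000 simulated trials per row.**

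| p | c | f0 / f1 (days) | Observed risk, control / prospective | Ratio | Test rejects |
|---|---|---|---|---|---|
| 10% | 1.0 | 84 / 84 | 0.100 / 0.100 | 1.00 | 5.0% |
| 10% | 0.8 | 84 / 84 | 0.081 / 0.100 | 1.24 | 11.3% |
| 10% | 0.6 | 84 / 84 | 0.061 / 0.100 | 1.63 | 32.8% |
| 10% | 1.0 | 56 / 84 | 0.068 / 0.100 | 1.47 | 23.8% |
| 20% | 1.0 | 84 / 84 | 0.200 / 0.200 | 1.00 | 4.9% |
| 20% | 0.8 | 84 / 84 | 0.163 / 0.200 | 1.22 | 16.7% |
| 20% | 0.6 | 84 / 84 | 0.125 / 0.200 | 1.60 | 55.5% |
| 20% | 1.0 | 56 / 84 | 0.138 / 0.200 | 1.45 | 39.8% |

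In the rows with unequal capture or follow-up, nearly all rejections go against the bundle.

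**Opposite direction.** If instead the prospective group has the shorter follow-up (84 control, 56 prospective, full capture), the expected ratio is 0.068/0.100 = 0.68 at p = 10% and 0.138/0.200 = 0.69 at p = 20%. This favours the bundle with no true benefit.

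**True benefit, r = 0.70.** The expected observed ratio is 0.88 at 80% capture, 1.15–1.16 at 60% capture, 1.05 at 56 versus 84 days with full capture, and 1.29–1.30 at 80% capture with 56 versus 84 days. The direction reverses roughly when c × f0/f1 falls below r; for the last case 0.80 × 56/84 = 0.53, which is below 0.70.

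**Repeat events, if events are the unit.** With equal true rates, mean 0.1–0.4 events per patient and variance-to-mean ratio 1.1–2.6 (assumed; 10,000 runs), type I error is 0.07–0.23 when event totals are tested against 2:1. It is 0.08–0.35 when events are entered as if they were patients.

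**What person-time repairs.** With r = 0.70, full capture and 56 versus 84 days, a rate comparison returns 0.70, where the ratio of proportions is 1.05. It does not repair detection: at 60% capture the expected rate ratio is still 0.70/0.60 = 1.17.

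**The case against.** A condensed article may leave the counting rule to a fuller document, and the usual two-group chi-square counts patients with at least one event. That stands. A reader might infer that independence is violated as planned, but the Data Analysis Plan names no unit. If patients are counted, repeat events cost only information.

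The plan does not disregard follow-up altogether. It has the 84-day completer analysis, and the 14-day floor is justified only by TTR estimation. This stands in part. However, completers are by definition survivors who stayed, so deaths within the window drop out of that analysis. Applied to safety, the 14-day floor would also remove early deaths.

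A reader might take "direct contact with the participant at outpatient clinic, home visits, or electronic or paper record review" as showing that prospective events are sought by home visits. That sentence concerns INR results and also lists record review. After stability and one further INR, care returns to the clinical team. Referral-clinic records are reviewed in both groups, and the Discussion claims high-quality case-note data, though without naming adverse events. The detection difference therefore rests on early contact and study recording against chart review. It is plausible but unmeasured.

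A reader might also infer a doubling against the bundle, for example 84/60 = 1.40 for follow-up times 1/0.70 = 1.43 for missed minor bleeds. Neither input is in the article, and the second applies a capture rate for minor bleeds to a composite that includes death. If minor bleeds were half of all events (assumed), detection would give 1/(0.5 + 0.5 × 0.70) = 1.18 and the product 1.65. Nor is the direction settled, because withdrawal after severe events could shorten prospective follow-up. It would also go too far to call every safety comparison uninterpretable, since deaths and hospital-treated events should be visible in both groups' records.

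**Conclusion.** The point holds as a fault in a method that the plan fixes. The chi-square test ignores time at risk where follow-up may vary from 14 to 84 days or less, and the completer analysis does not cure that. Controls' minor events may also be under-counted. Type I error clearly exceeds 5% under modest assumed departures: 11–17% at 80% record capture, and 24–40% at mean follow-up of 56 versus 84 days. These figures rest on assumed control risks of 10–20%, a constant hazard, and assumed capture and follow-up. The actual size and direction cannot be known from the article. The independence problem applies only if events are the unit. The change should be made, but it concerns a secondary outcome and leaves the TTR comparison untouched.

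**What to change.** - Count patients by first event, and state this as the unit.
- Replace the chi-square test with Kaplan-Meier and log-rank or a Cox model for time to first event, or a rate model with a log follow-up offset. Run it from day 0 in all recruited patients, not only those with at least 14 days.
- If the comparison is adjusted, name a few covariates collected in both groups, such as site and indication, as the number of events allows. The primary analysis is an unadjusted t test, so it supplies no covariate list to borrow.
- Base the between-group comparison on death and on bleeding or thrombosis leading to hospital care. This restriction is what addresses detection; person-time alone does not. Report minor bleeds descriptively.
- Confirm that event dates and last-contact dates are extracted in both groups. The data lists name adverse events but not their dates.

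The cost is fewer events in the restricted comparison, some extra date extraction from records, and analysis wording and code. The article reports formal analysis under way in February 2023, so the change should be dated, and labelled post hoc if event data had already been compared.
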